#### Analysis of the secondary outcomes

All secondary outcome measures will be analyzed in the ITT population (see section for definition). The following outcomes will be reported with median and interquartile range (with minimum and maximum values) in each study group and compared between the groups using Mann-Whitney’s test:Vasopressor-free day (secondary outcome #4)Normalized cumulative fluid balance (secondary outcome #7)Normalized cumulative UF_NET_ (secondary outcome #8)Ventilator-free day (secondary outcome #10)Hospital/ICU length of stay (secondary outcomes #12)

The secondary outcomes listed below will be reported longitudinally over time (from inclusion to H72) in the ITT population and compared between the study groups using mixed effects regression models with a fixed interaction of group by time, and a random effect with the patient identifier to account for the repetition of measurements, as well as an offset accounting for baseline values. In case of a significant interaction, a post hoc multiple comparison analysis between study groups will be performed, adjusted for the repetition of tests by the Tukey method.Number of hemodynamic instability episodes (secondary outcome #1)Number of hemodynamic instability episodes with preload dependence (secondary outcome #2)Hemodynamic parameters (secondary outcome #3)Total SOFA score and hemodynamic SOFA score (secondary outcome #5)PaO_2_/FiO_2_ ratio and extravascular lung water index (secondary outcomes #9)

The following categorical outcomes will be reported with count and percentage in each study group and compared between groups using the chi-squared or Fisher exact test: severe adverse events and adverse events of special interest, vital status (secondary outcome #6), and MAKE-90 (secondary outcome #11). Finally, no statistical test will be performed with secondary outcome #12. The hemodynamic profiles identified by the hemodynamic protocol of the intervention group will be reported in the supplemental results of the study.

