### Intervention description {11a}

#### Intervention strategy

Within 2 h after inclusion, the net ultrafiltration rate of the intervention group will be set to 100 ml h^−1^ or more (based on the clinician-in-charge decision and without exceeding 400 ml h^−1^) and maintained as such for the next 72 h. The targeted net ultrafiltration rate will aim to compensate the fluid input received by the patient over the same period of time and was estimated based on daily fluid input of 2500 ml reported in the IDEAL-ICU trial [18]. An UF_NET_ rate of 100 ml h^−1^ corresponds to a weight-corrected UF_NET_ rate of 1.2 ml kg^−1^ h^−1^ in an 80-kg patient, which was associated with improved outcome in a large observational study [14]. After H72 following inclusion, the UF_NET_ rate will be left at the discretion of the treating clinician.

In the intervention group, a hemodynamic protocol will allow the decrease or the cessation of the UF_NET_ based on the definition of threatening hemodynamic profiles described in SM3, Supplemental Fig. 1. In summary, the first part of the hemodynamic protocol uses a “routine” systematic assessment performed during nursing rounds every 4 h and comprising calibrated cardiac index values, arterial lactate levels, central venous pressure, and the results of a postural maneuver assessing preload dependence. Based on these hemodynamic elements, the protocol aims to maintain a UF_NET_ rate of 100 ml h^−1^ or more (green profiles, letters A, B, and D in the Protocol Figure) or half it (orange profiles, letters C, E, F, and I) or cease it (red profile, letters G and H) in case of threatening hemodynamic phenotypes. The hemodynamic profiles will be re-assessed at each nursing round, and the UF_NET_ rate re-adjusted accordingly. In the intervention arm, arterial lactate concentrations will be measured 8-hourly during the 72 h of the intervention period.

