#### Safety secondary outcomes (study population is given in brackets)

The number of hemodynamic instability episodes observed in both study groups between inclusion and 72 h after inclusion or death, whichever comes first. Hemodynamic instability is defined as the occurrence of de novo tachycardia (heart rate > 120 bpm), de novo hypotension (systolic or mean arterial pressure below clinician-defined target and requiring hemodynamic resuscitation), de novo or extension of mottles, or de novo decrease in cardiac output (negative change in cardiac index > 15%) [*ITT population*].The number of hemodynamic instability episodes (as defined above) associated with preload dependence (identified by a significant and positive increase in cardiac output following a postural maneuver), observed in both study groups between inclusion and 72 h after inclusion or death, whichever comes first [*ITT population*].Mean arterial pressure values, cardiac index, central venous pressure, arterial lactate concentration reported every 4 h, and the vasopressor administered dose reported every 24 h, in both groups, between inclusion and 72 h after inclusion or death, whichever comes first [*ITT population*].The number of vasopressor-free days in both study groups, quantified as the number of days alive without vasopressors, starting at the time of inclusion and censored at day 28 of inclusion. Vasopressor weaning will be defined if vasopressors are not required for a continuous period of 48 h or longer. A value of 0 is allocated if the patients died between inclusion and day 28. A value of 0 is also allocated if the patient is still receiving vasopressors at day 28 [24]. In case of multiple vasopressor weaning episodes, only the last weaning attempt will be considered [*ITT population*].Organ failure severity evaluated by the total SOFA score, composed of the sum of the 6 organ-by-organ subscores (neurologic, respiratory, hemodynamic, hepatic, hematologic, and renal), and the hemodynamic SOFA subscore, in both study groups. SOFA subscores are allocated a value between 0 (no failure) and 4 (highest degree of failure) and will be collected once a day from inclusion to H72 or death, whichever comes first [17] [*ITT population*].Vital status at H72, day 28, and day 90 after inclusion, collected from electronic medical files and hospital databases [*ITT population*].

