## Statistical methods

### Statistical methods for primary and secondary outcomes {20a}

#### General comments and descriptive analysis

All analyses will be performed using the R software for statistical computing (R Core Team). A *p* value < 0.05 will be considered significant.

Patients’ characteristics at enrollment will be reported in each study group to help evaluate allocation balance. Continuous variables will be reported using median and interquartile range (with minimum and maximum values) and compared between the groups using the Mann-Whitney test. Categorical variables will be reported using count and percentage (including missing values) and compared between the groups using the chi-squared test or Fisher exact test, as appropriate. Missing value count and percentage of each reported variable will be given.

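### For the 4-hourly hemodynamic parameters in secondary outcome #3, a single patient random effect leaves the gating group-by-time test open to inflation above 5%

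*Protocol article*

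**What the plan says.** Under Analysis of the secondary outcomes, outcomes #1, #2, #3, #5 and #9 are to be compared between arms with "mixed effects regression models with a fixed interaction of group by time", together with "a random effect with the patient identifier to account for the repetition of measurements" and "an offset accounting for baseline values". No random slope or residual correlation structure is named, and the coding of time is not given.

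The interaction test acts as a gate: "In case of a significant interaction, a post hoc multiple comparison analysis between study groups will be performed", with Tukey adjustment. The threshold is set under General comments and descriptive analysis: a p "value < 0.05 will be considered significant".

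Measurement frequency differs by outcome. Safety secondary outcome #3 has mean arterial pressure, cardiac index, central venous pressure and "arterial lactate concentration reported every 4 h, and the vasopressor administered dose reported every 24 h". The Intervention strategy section says that in the intervention arm "arterial lactate concentrations will be measured 8-hourly during the 72 h of the intervention period". SOFA scores (#5), and PaO2/FiO2 and extravascular lung water (#9), are daily.

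**The concern.** A random intercept implies the same correlation between any two readings from a patient, whatever the gap, and no patient-specific drift. For hemodynamic values recorded every 4 h over three days, neither assumption is credible. The protocol itself makes trajectories differ: the ultrafiltration rate is re-adjusted at each nursing round in the intervention arm, and vasopressors are titrated to targets set by the treating clinician.

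If neighbouring readings resemble each other, or patients drift at their own rates, the model counts within-patient readings as more independent information on the trend than they are. The standard error of the group-by-time term is then too small. Because that term opens the between-arm contrasts, a chance difference in a hemodynamic parameter, in either direction, gets through more often than one time in twenty. Tukey adjustment after the gate does not correct the gate. The Discussion says the trial is meant to help design a larger one, so a spurious signal could be carried forward.

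**Working it through.** **Inputs from the article.** Nominal level 0.05. 58 patients, so 58/2 = 29 per arm. Recruitment stops at 21 per arm with an assessable primary outcome. Readings to H72 including baseline: 72/4 + 1 = 19 (4-hourly), 72/8 + 1 = 10 (8-hourly), 72/24 + 1 = 4 (daily). If baseline enters only through the offset, the 4-hourly series has 18 points. The offset subtracts one constant per patient and cancels from within-patient comparisons, so it does not repair the problem.

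**Assumptions not in the article.** Gaussian outcome; intraclass correlation 0.5; AR(1) residual correlation ρ per 4 h from 0 to 0.9, or patient slopes with SD 0.25 to 1.0 total SD over 72 h; time either linear or categorical.

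**Tests compared, under no true effect.** In complete balanced data the random-intercept interaction test equals the within-patient test. With T time points, n per arm, centred times t and pooled within-patient residual variance s²:
- Linear time: slope difference / √(2s²/(n·t′t)), with 2n(T−1)−2 df.
- Categorical time: F = [SS(group×time)/(T−1)] / [SS(error)/((T−1)(2n−2))].
- Comparator: a t test on the per-patient slopes, with 2n−2 df.

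**Results: T = 19, n = 29, 6,000 replicates (Monte Carlo SE about 0.3 points at 5%).**

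| Setting | Linear, random intercept | Categorical, random intercept | Per-patient slopes |
|---|---|---|---|
| ρ = 0, parallel trends | 4.6% | 4.5% | 4.6% |
| ρ = 0.3 | 13.8% | 6.2% | 5.3% |
| ρ = 0.5 | 23.2% | 8.2% | 4.5% |
| ρ = 0.7 | 35.3% | 12.2% | 5.4% |
| ρ = 0.9 | 48.6% | 15.9% | 5.2% |
| ρ = 0, slope SD 0.25 | 7.3% | 5.4% | 4.9% |
| ρ = 0, slope SD 0.5 | 14.8% | 5.7% | 5.0% |
| ρ = 0, slope SD 1.0 | 31.3% | 7.4% | 5.1% |

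The first row recovers the plan's nominal 5%, which checks the method.

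**Closed-form check of the linear column.** Let R be the AR(1) correlation matrix, q = t′Rt/t′t, w = T − 1′R1/T, and E(s²) = (2nw − 2q)/(2n(T−1) − 2). The true variance of the slope difference is k = q/E(s²) times what the model believes, so type I error ≈ 2[1 − Φ(1.96/√k)].
- At ρ = 0.5: q = 2.382, 1′R1 = 53.0, w = 19 − 53.0/19 = 16.211.
- E(s²) = (58×16.211 − 2×2.382)/(58×18 − 2) = 935.5/1042 = 0.898.
- k = 2.382/0.898 = 2.65, and 1.96/√2.65 = 1.20, giving 22.9% (simulated 23.2%).
- At ρ = 0.3, 0.7 and 0.9, k = 1.74, 4.38 and 8.02, giving 13.8%, 34.9% and 48.9%.

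**Other designs.**
- 21 per arm, ρ 0.3 to 0.9: 13.9-49.7% linear, 6.4-15.1% categorical.
- 10 points (8-hourly, same ρ per 4 h), ρ 0.3 to 0.9: 6.4-32.8% linear, 4.2-11.2% categorical.
- 4 daily points, all settings: about 5-12% linear and 4-6% categorical. A separate set of 3,000-replicate runs gave 11-17% linear and 5.5-7% categorical, so the combined range is about 5-17% and 4-7%.

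**With deaths.** With the article's expected 25% mortality by H72, 29 per arm, ρ = 0.5 and linear time, the fitted random-intercept model rejected in 21% and a random-slope model in 5.7%. These are 300 replicates with many convergence warnings, so they are approximate.

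**The case against.** The best counter-argument is that this is one condensed sentence in a journal article. Residual structure, slopes and degrees of freedom are often left to an analysis plan, which is not shown, and a random effect grouped by patient does not strictly exclude a slope. That stands as a caution. It does not remove the point, because the sentence names the device meant to handle repetition, and its natural reading gives standard errors that are too small.

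Three stronger readings are tempting, and the document does not support them.
- A reader might infer that the test does run far above 5%. The article gives no autocorrelation, slope variance or coding of time. The largest figures need linear time, whereas post hoc Tukey contrasts fit categorical time better; there the range is about 6-16%, and patient slopes alone give only 5.4-7.4%.
- A reader might infer that all the outcomes sent to this model are affected alike. SOFA, PaO2/FiO2, lung water and vasopressor dose are daily, and near nominal with categorical time. Lactate is 8-hourly in the intervention arm. The episode counts (#1, #2) were not simulated.
- A reader might infer that this test drives the hemodynamic safety conclusion. The Safety secondary objectives tie hemodynamic safety first to the number of instability episodes. The 4-hourly parameters are a separate objective, though still listed under safety.

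The warning about convergence in a trial of 58 patients is also fair, and it is why the fix needs a fallback.

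**Conclusion.** The point holds in conditional form. For mean arterial pressure, cardiac index and central venous pressure, and partly for lactate, the stated structure ignores serial correlation and patient-specific trends, and the gating test is open to inflation. The size depends on two things the article does not give, the coding of time and the autocorrelation; the ranges in the table rest on assumed values and Gaussian data. The excess for daily outcomes is small, especially with categorical time, and no figure is claimed for the counts. The primary outcome uses a Mann-Whitney test and is not touched. The change is worth making before database lock, but it concerns a secondary outcome.

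**What to change.** In the section on analysis of the secondary outcomes:
- State whether time is categorical or linear.
- For the 4-hourly parameters in #3, keep the patient random intercept and add a continuous-time AR(1) residual correlation; if time is linear, also add a patient random slope. Continuous time also accommodates 8-hourly lactate.
- Use small-sample degrees of freedom where the software supports them.
- Pre-state a fallback for non-convergence, for example a between-arm comparison of per-patient slopes, which stayed at about 5% in every setting tried.

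The cost is a sentence or two of text and a few lines of R. The downside is somewhat wider intervals and possible convergence problems. The slope fallback tests only a linear trend, and the check of the remedy covers linear time only; the AR(1) model with categorical time was not simulated.

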#### Efficacy secondary outcomes (study population is given in brackets)

7.Normalized cumulative fluid balance measured in both groups at H24 and H72 after inclusion or death, whichever comes first, and at day 7 in alive patients. Fluid balance measured between inclusion and early time point (H24 or H72 or death) will be normalized by dividing it by the observation period duration and expressed in ml h^−1^. The fluid balance at H24 and H72 will be quantified using the same input and output items as per the primary outcome. The fluid balance at day 7 will be estimated based on the change in body weight between inclusion and day 7 [*ITT population*].8.Normalized cumulative UF_NET_ volume in both study groups at H24 and H72 after inclusion or death, whichever comes first. Cumulative UF_NET_ measured between inclusion and H24 or H72 or death will be normalized by dividing it by the observation period duration and expressed in ml h^−1^. The cumulative UF_NET_ volume will be computed based on the UF_NET_ volumes reported every 4 h between inclusion and 24 or 72 h after inclusion or death, whichever comes first [*ITT population*].9.PaO_2_ to FiO_2_ ratio and the extravascular lung water index measured with the cardiac output monitoring device, measured once a day from inclusion to H72 or death, whichever comes first. The FiO_2_ is the FiO_2_ set on the respirator or the high-flow nasal cannula device. In non-ventilated patients, the FiO_2_ will be estimated using the following formula: FiO_2_ = 0.21 + 0.03 × oxygen flow rate (in L min^−1^) [25] [*ITT population*].10.The number of ventilator-free days in both study groups, quantified as the number of days alive without mechanical ventilation, starting at the time of inclusion and censored at day 28 of inclusion. Mechanical ventilation weaning will be defined if invasive mechanical ventilation is not required for a continuous period of 48 hours or longer. A value of 0 is allocated if the patients died between inclusion and day 28. A value of 0 is also allocated if the patient is still receiving invasive mechanical ventilation at day 28 [24]. In case of multiple mechanical ventilation weaning episodes, only the last weaning attempt will be considered [*ITT population*].11.MAKE-90 assessed between inclusion and day 90 after inclusion in both groups. MAKE-90 comprises death before or at day 90, RRT dependence at day 90, and persistent stage 2 or 3 acute kidney injury (as per the KDIGO guidelines) at day 90. RRT dependence is present if the patient is still receiving CRRT at day 90 or if he has received an intermittent technique in the time frame of ±2 days around day 90. Persistent acute kidney injury is adjudicated based on a baseline plasma creatinine concentration (identified in the 6 months to 7 days before ICU admission), and the plasma creatinine measured at day 90 [6]. In case of missing baseline creatinine value, it will be retrospectively estimated [26]. Each element of the composite event will be evaluated separately [*ITT population*].12.Hospital and ICU length of stay, quantified as the duration, in days, between inclusion and hospital and ICU discharge (alive or deceased), respectively [*ITT population*].

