### Sample size {14}

We make the hypothesis that the fluid balance will be of 4000 ± 4000 ml at H72 of inclusion in the control group and that the intervention strategy will generate a fluid balance of 0 ± 4000 ml at H72 of inclusion (absolute between groups difference of 4000 ml). The hypothesis is based on the data reported by a large randomized controlled trial evaluating the timing of RRT in the ICU, in which the H72 cumulative fluid balance was 3711 ml in the early arm and 3917 ml in the delayed arm of the study [18]. Based on this hypothesis, the required sample size to compare two means between two equally sized samples (and a bilateral hypothesis), with a *⍺* of 0.05 and a power 1–*β* of 0.8, would be 16 patients per arm, hence a total of 32 patients. Since (1) we expect a non-survival rate of 25% at 72 h of inclusion (corresponding to the time point of the primary outcome evaluation) and (2) the expected distribution of the primary outcome would not follow the normal distribution, justifying an increase of 25% in sample size, the final total number of patients to enroll would be 58, equally distributed between study groups. Patients deceased before 72 h of inclusion, or alive at H72 but with a missing primary outcome measure, will not be included in the analysis of the primary outcome. Once the required number of 21 patients per arm with an assessable primary outcome will be reached, inclusions will cease.

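### A single baseline offset is prescribed for all longitudinal secondary outcomes: it has no meaning for the episode counts, where exposure time is needed, and costs precision for the other outcomes

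*Protocol article*

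**What the plan says.** The protocol article, under Analysis of the secondary outcomes, sends five secondary outcomes to one model: episode counts (#1), preload-dependent episode counts (#2), hemodynamic parameters (#3), SOFA scores (#5), and PaO2/FiO2 with lung water (#9). The model is "mixed effects regression models with a fixed interaction of group by time, and a random effect with the patient identifier", "as well as an offset accounting for baseline values". The next step is conditional: "In case of a significant interaction, a post hoc multiple comparison analysis between study groups will be performed", with Tukey adjustment.

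Under Safety secondary outcomes, #1 is "The number of hemodynamic instability episodes observed in both study groups between inclusion and 72 h after inclusion or death, whichever comes first". Outcome #2 has the same window.

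Under Efficacy secondary outcomes, the early fluid balance (#7) "will be normalized by dividing it by the observation period duration", and cumulative net ultrafiltration (#8) is treated the same way. No such step is given for #1 or #2.

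Under Sample size, "we expect a non-survival rate of 25% at 72 h of inclusion".

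**The concern.** An offset is a term whose coefficient is fixed at 1. That raises three questions.

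- **Counts.** A count that starts at inclusion has no earlier value to use as an offset. The offset that a count model usually needs is log time at risk, and here that time is cut short by death.
- **Other outcomes.** Fixing the baseline slope at 1 turns the analysis into change from baseline, when the data could estimate the slope.
- **Reporting.** The text names an interaction and conditional post hoc contrasts, but no average difference between arms. The first safety objective is to compare the number of episodes over the first 72 h, which is an overall contrast.

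Outcomes #1 and #2 are the main hemodynamic safety comparison of a strategy whose acknowledged risk is hemodynamic instability. A count that ignores exposure errs towards the arm with more early deaths.

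**Working it through.** The plan states no figure for these models, so there is none to reproduce. From the document come the 72 h window, the end of counting at death, 25% expected mortality by H72, and 58 patients (29 per arm). The assumptions are arm-specific mortality, the timing of deaths, the interval length for episode counts, and the correlation r between baseline and follow-up.

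**1. The offset for #1 and #2.** Counting starts at inclusion, so the baseline count is absent, or zero by construction. Under a log link the offset would be log(0), which is undefined. Under an identity link an offset of 0 changes nothing. Neither form accounts for exposure.

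**2. Size of the exposure artefact.** Assume equal hourly episode rates in both arms, a share d of patients dying evenly over 72 h, and d = 0.25 v 0.40 (the second value is assumed).

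| How episodes are counted | d = 0.25 | d = 0.40 | Ratio | Artefact |
|---|---|---|---|---|
| One total: mean hours, 72(1−d) + 36d | 63.0 | 57.6 | 0.914 | 8.6% |
| Daily: exposure per interval begun, (3 − 1.5d)/(3 − d) | 2.625/2.75 = 0.955 | 2.4/2.6 = 0.923 | 0.967 | 3.3% |
| 4-hourly: (18 − 9d)/(18 − 8.5d) | 15.75/15.875 = 0.992 | 14.4/14.6 = 0.986 | 0.994 | 0.6% |

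In the interval versions, intervals after death contribute no rows, so only the interval of death has short exposure.

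As a second check for one total per patient, take a constant hazard, with mean time at risk 72d/(−ln(1−d)).
- At 25% mortality this is 62.6 h, or 87% of 72 h.
- At an assumed 15% v 35% the count ratio is 58.5/66.5 = 0.88.
- At an assumed 20% v 30% it is 0.94.

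A rate model returns 1.00 in every case.

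**3. Precision for #3, #5 and #9.** With equal variances s² at baseline and follow-up, the variance of a between-group difference at one time is proportional to 2s²(1−r) with the offset and s²(1−r²) with a covariate. The ratio is 2/(1+r).

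| Assumed r | 0.3 | 0.5 | 0.7 | 0.9 |
|---|---|---|---|---|
| Variance ratio, offset/covariate | 1.54 | 1.33 | 1.18 | 1.05 |

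At r = 0.5 the confidence interval is √1.333 = 1.155 times as wide, and 29 per arm are worth 29 × 1.5/2 = 21.8. Below r = 0.5, 2(1−r) exceeds 1, so the offset does worse than ignoring baseline. A mixed-model simulation (300 runs, 29 per arm, three post-baseline times, r = 0.5) gave a ratio of 1.32, with mean standard errors of 0.261 v 0.227.

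In the same simulation the interaction estimates agreed to rounding error. A constant offset cancels within a patient, so the interaction test loses nothing when only post-baseline rows are modelled. If the inclusion value is also a response row, subtracting baseline makes that row zero for everyone. The interaction then becomes a change-score contrast, and the loss applies to it too.

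**4. Steady differences.** A constant excess over 72 h produces no group-by-time interaction among post-inclusion values. If the inclusion value is a response row, a steady later difference does appear as an interaction. The counts have no such row.

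**The case against.** **Between-arm comparison.** A reader might infer that arms are compared only when the interaction is significant, so that constant harm is never tested. The text does not say that. It says the outcomes are compared by the mixed models and makes only the post hoc contrasts conditional. It also speaks of values from inclusion to H72, and on that reading a steady effect on #3, #5 or #9 can show as an interaction. This objection stands. What remains is that no average effect is named, so one may go unreported, above all for the counts.

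**Exposure.** The largest figure needs one total per patient. The model is longitudinal with a random patient effect, which suggests interval counts and a much smaller artefact. This also stands. However, the outcome definition describes a single total to H72 or death, and no interval is given, so the full range applies.

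**Other safety comparisons.** Excess deaths would not go unseen. Mortality is compared at H72, day 28 and day 90, H72 mortality is reviewed after 20 patients, and adverse events and vasopressor-free days are compared between arms. This lowers the stakes but does not correct the episode comparison.

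**Detail left elsewhere.** Link, count distribution and exposure term may be in a fuller document, and their absence alone would be no finding. The protocol article does, however, state which offset to use, and that choice does not fit #1 and #2.

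**Change scores.** They are unbiased under randomisation. This stands: for #3, #5 and #9 the issue is precision only.

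**Conclusion.** The concern holds at moderate severity.

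- For #1 and #2 the prescribed offset is either undefined or idle, and exposure ending at death is not handled. This follows from the text alone. The size of any artefact depends on assumptions: zero if mortality is equal, and at 25% v 40% about 9%, 3% or under 1% according to the counting interval. The documents give only 25% overall and do not support any particular difference between arms, so 9% is not an expected bias.
- For #3, #5 and #9 the offset inflates the variance of between-group differences by 54% to 5% for r from 0.3 to 0.9. The correlations are assumed, and the loss is small where r is high.
- A steady difference may go without an estimate. The documents do not support the stronger claim that it is never tested.

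The primary outcome has its own Mann-Whitney test and is not affected.

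**What to change.** Rewrite the paragraph on longitudinal outcomes as follows.

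- **#1 and #2:** a Poisson or negative-binomial model with log(hours observed to H72 or death) as offset and no baseline term, reporting the rate ratio with its 95% confidence interval. If episodes are counted by interval, state the interval and use the hours observed within it.
- **#3, #5 and #9:** baseline value as a covariate, with only post-baseline values as responses.
- **All five:** report the average between-group difference (rate ratio for #1 and #2) over 72 h with its confidence interval, whatever the interaction shows. Keep the Tukey-adjusted contrasts as a supplement.

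The cost is one reworded paragraph and slightly different model code. The baseline values and times of death are already collected, so no new data are needed.

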### Trial design {8}

The GO NEUTRAL study is a multicenter, open-labeled, randomized, controlled, superiority trial with parallel groups and balanced randomization with a 1:1 ratio. The first version of the protocol was published on March 3, 2021, before the first inclusion (Supplemental Material 1, French version). The WHO Trial Registration Data Set is provided in Supplemental Material 2.

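### Tukey's method does not fit post hoc comparisons of two arms over time: within time points it corrects nothing, and over all group-by-time cells it is valid but needlessly strict

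*Protocol article*

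**What the plan says.** The protocol article, under Analysis of the secondary outcomes, compares five sets of longitudinal outcomes from inclusion to H72: instability episodes, preload-dependent episodes, hemodynamic parameters, SOFA scores, and PaO2/FiO2 with lung water. It uses "mixed effects regression models with a fixed interaction of group by time", a patient random effect, "as well as an offset accounting for baseline values". It continues: "In case of a significant interaction, a post hoc multiple comparison analysis between study groups will be performed". The same sentence then says how multiplicity is to be handled; these comparisons are "adjusted for the repetition of tests by the Tukey method".

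Other parts of the article fix the setting:

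- Trial design describes "parallel groups and balanced randomization with a 1:1 ratio", so there are two arms.
- General comments and descriptive analysis states: "A *p* value < 0.05 will be considered significant".
- Safety secondary outcomes gives the timing of the hemodynamic set (arterial pressure, cardiac index, central venous pressure and lactate, then vasopressor dose): "arterial lactate concentration reported every 4 h, and the vasopressor administered dose reported every 24 h".
- SOFA, PaO2/FiO2 and lung water are daily.

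**The concern.** Tukey's method protects all pairwise differences among a set of means. The comparison named here is one difference, intervention versus control, repeated over time. These are two different families. Tukey can be applied in two main ways, and neither protects the family that the sentence describes. Two analysts could both follow the text and report very different adjusted p-values.

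At stake are statements about when the arms diverged in pressure, cardiac index, lactate or SOFA. Several of these are listed as safety outcomes, and the trial is meant to inform a larger one.

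**Working it through.** The plan gives no number of comparisons, adjusted level or error rate for these tests, so there is no stated figure to reproduce.

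**Inputs from the article.** Two arms; alpha 0.05 (two-sided assumed here); 58 patients, so 29 per arm. A 4-hourly grid from H0 to H72 has T = 72/4 + 1 = 19 points, or 18 if H0 enters only as the offset. A daily grid has T = 4, or 3. Lactate is 4-hourly in the outcome list but 8-hourly in the description of the intervention arm; at 8 hours T = 10, or 9. No time grid is stated for the episode counts, so nothing is computed for them.

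**Assumptions.** Correlation between time points, the size of the true effects, and the degrees of freedom.

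**Reading A: Tukey within each time point.** The critical |t| is the 0.95 studentized-range quantile for k means, divided by √2. For k = 2 and 56 df this is 2.003, the same as the unadjusted t (1.960 for large df). Nothing is corrected across time.

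The familywise error must be taken with the interaction condition in place. Correlated between-arm z-scores were simulated with common correlation 0, 0.5 or 0.8. Post hoc tests counted only when the interaction test was significant at 5%.

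- *No difference at any time:* error is about 2-5% for T = 18 or 19, and about 1-5% for T = 3 or 4.
- *Real effect in the last third of times (expected z = 3.5):* error at the remaining null times is as follows.

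| Grid | Correlation 0 | 0.5 | 0.8 |
|---|---|---|---|
| T = 19 | 48% | 34% | 19% |
| T = 18 | 46% | 32% | 19% |
| T = 4 | 12% | 12% | 10% |
| T = 3 | 7% | 8% | 8% |

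As a hand check, T = 18 leaves 12 null times. If these are independent and the interaction is almost always significant, 1 − 0.95^12 = 46%, which agrees.

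**Reading B: Tukey over all group-by-time cells.** There are 2T cells and 2T(2T − 1)/2 pairs, of which only T are same-time between-arm contrasts. Critical values are for 200 df.

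| Grid | Cells | Pairs | Relevant pairs | Critical absolute t |
|---|---|---|---|---|
| 4-hourly, with H0 | 38 | 703 | 19 | 3.92 |
| 4-hourly, without H0 | 36 | 630 | 18 | 3.90 |
| Daily, with H0 | 8 | 28 | 4 | 3.06 |
| Daily, without H0 | 6 | 15 | 3 | 2.88 |

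For 8-hourly lactate there would be 190 or 153 pairs.

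**Adjustment limited to the 18 between-arm contrasts.** Max-t critical values come from multivariate normal draws with correlation ICC + (1 − ICC)ρ^lag. They are 2.70 for ICC 0.5 and ρ 0.8, 2.91 for ICC 0.3 and ρ 0.5, and 2.99 for independence. The Bonferroni value, which is also Holm's first step, is 2.99.

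**Power at one 4-hourly time.** For an assumed 0.8 SD difference with 29 per arm, the expected z is 0.8/√(2/29) = 3.05. By normal approximation, power is Φ(3.05 − c):

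- c = 2.70, 2.91 and 2.99 give 64%, 55% and 52%.
- c = 3.90 and 3.92 give 20% and 19%. The large-df values 3.84 and 3.86 give about 21%, so the choice of df matters little.

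These are powers for a single contrast, before the interaction condition is applied.

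**Error after the fix.** In the same simulations, Bonferroni over the T between-arm contrasts holds error at the null times to about 1.5-3.4%.

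**The case against.** The strongest reply is that the interaction condition already protects these tests. A reader might infer error rates of 26-45%, or 60% under independence, for 18 unadjusted contrasts. Those rates describe contrasts run unconditionally when the arms never differ, which the article does not plan; with the condition, that error is near or below 5%. This stands. What remains is that the condition protects only that one situation. Once some times truly differ, the others are unprotected, and that is when the post hoc tests are used.

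A reader might also infer that about 700 irrelevant pairs are involved throughout. The documents support that only for the 4-hourly variables. Daily outcomes have 15-28 pairs and the excess strictness there is moderate.

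Nor do the documents support saying that hemodynamic harm would be missed. Tukey over all cells is valid and costs only power to locate a difference in time. The interaction test is the main between-arm inference, and harm is also followed through instability episodes, adverse events, mortality and an interim look at H72 mortality.

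Finally, the choice of contrasts and time coding is commonly left to an analysis plan. That is fair for the detail. But the article does name a method and its purpose, and the method does not serve that purpose.

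**Conclusion.** The point holds as a minor correction. Tukey either leaves the repetition over time uncorrected or corrects for mostly irrelevant pairs. The article does not say which, so neither consequence can be called the planned one. The first reading inflates error only when the arms differ at some times, strongly for 4-hourly variables and modestly for daily ones. The second loses power and creates no excess of false positives.

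The error figures depend on the assumed correlations and on a true effect of z = 3.5 in the last third of times. The power figures depend on the assumed 0.8 SD and full arms of 29. That Tukey for two means equals the t test needs no assumption. The primary analysis, a Mann-Whitney test of H72 fluid balance, is untouched.

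**What to change.** Replace the reference to Tukey with one sentence. For each longitudinal outcome, the family is the set of same-time, post-inclusion between-arm contrasts (18 for a 4-hourly variable, 3 for a daily one), adjusted by the single-step multivariate-t (max-t) method from the fitted model, or by Holm. Either method controls error across that family even when some times truly differ, so the interaction condition can stay or go. The choice should be fixed before database lock. The cost is one sentence in the analysis section or the analysis plan, with no change to data collection, sample size or the primary analysis.
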